## Abstract

**Background:**

Cardiovascular diseases (CVD) are the leading cause of mortality. In 2014, they were responsible for 38.9% of all causes of death in Germany. One major risk factor for CVD is a lack of physical activity (PA). A health-promoting lifestyle including regular PA and minimizing sitting time (ST) in daily life is a central preventive measure. Previous studies have shown that PA decreases in older age; 2.4–29% of the people aged over 60 years achieve the World Health Organization recommendations. This age group spends on average 9.4 h per day in sedentary activities.

To increase PA and decrease ST, a low-threshold intervention, consisting of individualized feedback letters based on objectively measured data of PA and ST, was developed. The research question is: Do individual feedback letters, based on accelerometer data, have a positive effect on PA and ST?

**Methods/design:**

MOVING is a two-arm, randomized controlled trial. Inclusion criteria are age ≥ 65 years and the ability to be physically active. Exclusion criteria are the permanent use of a wheelchair and simultaneous participation in another study on PA.

At baseline participants who give informed consent will receive general information and recommendations about the positive effects of regular PA and less ST. Participants of both groups will receive an accelerometer device, which records PA and ST over a period of seven consecutive days following by a randomization. Participants in the intervention group will receive automatically generated, individualized feedback letters by mail based on their PA and ST at baseline and at 3-month follow-up. Further follow-up examinations will be carried out at 6 and 12 months.

The primary outcome is the increase of PA and the reduction of ST after 6 months in the intervention group compared to the control group.

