### Research objectives

The primary objective of the MOVING study is to examine the effects of an increase of PA and a reduction of ST after 6 months in the intervention group compared to the control group as assessed by accelerometry.

Secondary outcomes are whether there is an improvement of blood pressure, a reduction in weight and waist circumference as well as an increase of self-reported time doing PA, self-reported ST, and self-reported time doing PA as well as the effect of feedback letters on self-efficacy after 6 and 12 months.

Additionally, the impact of personal feedback letters on lifestyle (household, gardening, free time, and sport activities), quality of life and type of PA will be evaluated by questionnaire in the intervention group compared to control group after 6 and 12 months.

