### Power calculation

The sample size estimate was based on the amount of PA (mean time in min per day), measured in a comparable group of elderly people. In the study in question (Troiano et al.) the amount of PA was on average 15 min of combined PA (moderate and vigorous PA) per day [21]. We took these data as the starting point for the estimation of the required sample size. We assume that participants in the control group remain at approximately the same level while people in the intervention group increase their amount of PA by 20% [42], which corresponds to an increase from 15 to 18 min of PA per day after 6 months. To demonstrate this effect, a total number of 151 participants is needed (standard deviation 6.0 min, alpha = 0.05, power = 0.80). Assuming a loss to follow-up of about 30%, we will recruit 216 participants.

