### Data analysis

ActiLife software (version 6.13.2 or later, ActiGraph, Pensacola, FL, USA) will be used for data download and data processing. A valid measurement day is defined as a record of at least 10 h total wearing time and a record time of at least 4 days is required for data analysis. To categorize PA intensity, we used specific cut points based on Freedson [45]. PA is divided into sedentary (0–99 steps), light (100–1951 steps), moderate (1952–5724 steps), and vigorous (5725–9498 steps) PA. Step counts are based on 60-s epochs.

Statistical analysis will be conducted using pseudonymized data. First, the assessed project data will be descriptively analyzed. We will verify the conditions in both groups. In case of significant differences between the intervention and control group, analyses will be adapted accordingly and adjusted for relevant variables. Subsequently, the primary and secondary outcomes will be analyzed between the groups using *t* tests or corresponding non-parametric tests in case of ordinal variables or non-normality of the values. The tests will be conducted based on the intention-to-treat principle. The use of the intention-to-treat procedure ensures that each subject is included in the analysis. The analysis are carried out with the statistical software IBM SPSS Statistics (version 23.0.0.2 or later, IBM Corp., Armonk, NY, USA).

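### PA and ST at 6 months are jointly primary, but alpha = 0.05 and power = 0.80 are established for MVPA only, and no either/both rule is given

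*Protocol article*

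**What the plan says.** The article treats two accelerometer outcomes as primary.

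- Abstract, Methods/design: "The primary outcome is the increase of PA and the reduction of ST after 6 months in the intervention group", compared with the control group.
- Research objectives: the primary objective is "to examine the effects of an increase of PA and a reduction of ST after 6 months in the intervention group", compared with control and assessed by accelerometry.
- Power calculation: "The sample size estimate was based on the amount of PA (mean time in min per day"). The starting value is "on average 15 min of combined PA (moderate and vigorous PA) per day", the target is a 20% rise, "which corresponds to an increase from 15 to 18 min of PA per day after 6 months", and the remaining inputs are "standard deviation 6.0 min, alpha = 0.05, power = 0.80". This gives 151 participants, raised to 216 for about 30% loss to follow-up.
- Abstract, Discussion: the target effect is again given for MVPA only.
- Data analysis: "the primary and secondary outcomes will be analyzed between the groups using" t tests, or non-parametric tests for ordinal or non-normal data.

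No section gives an assumed effect or standard deviation for ST. None says whether the primary claim needs both outcomes or only one, in what order they are tested, or how alpha is shared. Sidedness is not stated.

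**The concern.** One alpha and one power are given for a primary claim that has two parts, and both figures come from only one of the parts. What they are worth for the whole claim depends on a rule that the article does not state.

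The practical risk is a split result. If MVPA rises significantly and ST does not fall, or the reverse, nothing in the text says whether the trial succeeded. That decision could then be made after the data are seen. Whatever the rule, the ST half of the primary outcome has no planning assumptions behind it.

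**Working it through.** **Inputs.** From the power calculation: difference 18 − 15 = 3 min/day, SD 6.0, so d = 3/6 = 0.5; alpha 0.05; power 0.80; 151 evaluable. Allocation is 1:1, so 75.5 per arm. Assumed here: two-sided tests; the correlation between the two test statistics (0 to 0.9); the ST standardised effect (0.5 or 0.3).

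**The plan's own figure.** n per arm = 2(1.960 + 0.842)²/0.5² = 62.8, so 63 per arm and 126 in total. The exact t test gives 64 per arm, 128 in total. The stated 151 is larger than its inputs require. The dropout step does reproduce: 151/0.70 = 216. What matters here is the power of the PA test at 151. The expected test statistic is 0.5 × √(75.5/2) = 3.07, and Φ(3.07 − 1.96) = 86.7%, or 86.3% by the t test.

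**If either outcome suffices, each tested at 0.05.** The two-sided familywise error is P(|Z₁| > 1.96 or |Z₂| > 1.96) under the null. With independent tests it is 1 − 0.95² = 9.75%. In the beneficial direction alone it is 1 − 0.975² = 4.9%, against 2.5% for one test. For correlated tests, from the bivariate normal:

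| Correlation | Two-sided | Beneficial direction only |
|---|---|---|
| 0 | 9.75% | 4.9% |
| 0.5 | 9.1% | 4.5% |
| 0.7 | 8.3% | 4.2% |
| 0.9 | 7.0% | 3.5% |

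Power to succeed under this rule is at least that of PA alone, about 86%.

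**If both are required, each tested at 0.05.** Type I error stays at or below 0.05. Joint power is the bivariate normal probability that both tests succeed, with PA at 86.3%:

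- ST d = 0.5 (86.3% alone): 0.863² = 74% at correlation 0, rising to 82% at 0.9.
- ST d = 0.3 (44.9% alone): 0.863 × 0.449 = 39% at correlation 0, rising to 45% at 0.9.

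**Sensitivity to the unexplained 151.** An SD of about 6.6 would give 151 at exactly 80% power. If that were the true SD and ST also had 80%, joint power would be 0.80² = 64% at correlation 0 and 75% at 0.9. The article states 6.0, so the main results use 6.0.

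**Cost of an alpha split.** With 0.025 for each outcome, d = 0.5 and 151 evaluable, PA power is Φ(3.07 − 2.24) = 79.7%, or 79.0% by the t test. Reaching 80% takes 154 (normal approximation) or 156 (t test, 78 per arm) evaluable, which is 3 to 5 more.

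**The case against.** **The word "and".** The primary outcome is written in the singular with a conjunction, so requiring both is the more natural reading. On that reading no alpha inflation is shown. This stands: the 7.0% to 9.75% is conditional on an either-suffices rule that the text does not state. It also counts significant results in the harmful direction, whereas the stated aim is directional.

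**Power was claimed for PA only.** The power calculation attaches 0.80 to the rise from 15 to 18 min and does not claim joint power. This is also correct. It confirms that ST was left out of the sizing even though it is part of the primary outcome.

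**The rule may be in the SAP.** A testing order or alpha split is commonly left there, and this is a condensed article, so the absence of a multiplicity procedure would not be a finding by itself. What is fixed in this text is which outcomes are primary and which one the trial was sized on, and these do not match. A later adjustment method would not supply the missing ST assumptions.

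**A stronger reading.** A reader might infer that the stated alpha and the stated power both fail. The document does not support this, because no single rule breaks both. Under "either", error rises but power is at least that of PA. Under "both", alpha holds and only power is affected. Nor can 64% be taken as the joint power: it assumes exactly 80% for each test, while the stated inputs with 151 evaluable give PA about 86%, and the ST value is unknown.

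**Conclusion.** The mismatch is real and is fixed in the article: two outcomes are primary, and alpha and power are established for one of them. Which property fails to describe the primary claim depends on the unstated rule.

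- Either suffices: the type I error exceeds its nominal level, by less than a factor of two.
- Both required: the error rate is sound, but joint power is not the stated 80% and cannot be determined. It could lie close to 80% if ST responds as strongly as MVPA is assumed to, or below 50% if the ST effect is modest.

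The ST effects and the correlations are illustrative assumptions, and the tests are taken as two-sided. The severity is should-fix: the primary claim needs a stated rule, but the MVPA comparison itself is adequately sized on the stated inputs.

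**What to change.** Choose one option before any 6-month data are analysed, and record it as a dated change in the trial register.

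(a) Name accelerometer MVPA in minutes per day at 6 months as the single primary outcome, since the trial was sized on it. Test ST at 6 months next in a fixed sequence, at two-sided 0.05, only if MVPA is significant. This holds the familywise error for the two outcomes at 0.05 and needs no extra participants. The cost is that ST becomes a key secondary outcome, which changes the stated objective of a registered trial already recruiting.

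(b) Keep both as primary and state the rule:
- Both required, each at two-sided 0.05. No alpha split is needed and the objective is preserved. State the assumed ST effect, SD and correlation, and report the resulting joint power.
- Either sufficient, with Holm or Bonferroni (0.025 each). MVPA power is then about 79% at 151 evaluable with the stated SD. If the larger SD implied by 151 were true, it would be Φ(2.80 − 2.24), about 71%. ST power still needs its own assumptions.

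Under (b) the cost is a less favourable stated power. Either option takes a sentence in the objectives and one in the data analysis section; (b) also needs a revised power paragraph. State the sidedness of the tests at the same time.

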**Discussion:**

The goal of the study is to examine the effects of a simple feedback intervention on PA and ST in elderly people. We aim to achieve an effect of 20% increase in moderate-to-vigorous physical activity (MVPA). The intervention may have the potential to decrease crucial cardiovascular risk factors and, therefore, contribute to prevention of CVD.

**Trial registration:**

German Clinical Trials Register, ID: DRKS00010410. Registered on 17 May 2017.

**Electronic supplementary material:**

The online version of this article (10.1186/s13063-017-2425-2) contains supplementary material, which is available to authorized users.

## Background

Older age is associated with increasing risk for chronic diseases and multimorbidity [1–3]. The prevalence of cardiovascular diseases (CVD), including coronary heart disease (CHD) and stroke, increases with age [4]. In 2014, CVD were the leading cause of mortality [5] and responsible for 38.9% of all causes of death in Germany [6]. CVD produce substantial disabilities and reduce well-being [7, 8]. Therefore, older people are a relevant target group for effective and practicable strategies for CVD prevention [9].

According to the World Health Organization (WHO), lack of PA is an important risk factor for mortality [10] and is associated with a series of non-communicable diseases (NCD), e.g., type 2 diabetes and a number of cancers (e.g., colon cancer and breast cancer) [7]. Several studies have shown that a health-promoting lifestyle, including promotion of PA and reduction of ST, is correlated with improved overall health status [7, 11]. Furthermore, regular PA is a resource for physical and mental health and reduces risks of obesity and musculoskeletal system problems. Regular PA significantly decreases overall mortality by 22–34% and CVD mortality by 27–35% [12].

In general, international PA guidelines do not recommend that elderly people do less PA than younger adults [13–15]. The WHO recommends 150 min of moderate or 75 min of vigorous PA, or a corresponding combination of weekly PA for both for younger adults (aged 18–64 years) and older people aged over 65 years. PA should be done in time periods (bouts) of at least 10 min [14].

Recent academic literature points out that PA decreases in older age [16–18] while the amount of ST increases to high levels (about an average of 60% ST of waking time) [19, 20]. In Germany, 19.3% of men and 16.8% of women aged 60–69 years achieved the WHO recommendations. In the age group 70–79 years the amount of PA declines to 16.5% of men and 11.0% of women [10]. A study from the United Kingdom showed that 19% of men and 14% of women aged 65–74 years reach the recommended 30 min of moderate PA at least five times a week [7]. Data from Norway showed similar results among older people: 29% of men and 25% of women aged 65–69 years met the Norwegian PA recommendations (minimum of 30 min of daily PA of moderate intensity). In the age group 80–85 years the amount of PA declines; 7.1% of women and 3% of men reached the recommendations [9].

The National Health and Nutrition Survey (NHANES, USA) showed that 2.4% of people aged over 60 years achieved WHO recommendations for PA [21]. This age group spends on average 8.4 h (60–69) and 9.3 h (70–85) per day in sedentary activities (measured by accelerometer) which correspondents up to 70% of their wake time [19]. A systematic review of adults aged 60 years and older showed similar results: older people spend an average of 9.4 h doing sedentary activities which corresponds to 65–80% of their waking day. It is particularly striking that estimated self-reported ST is lower than objectively measured: on average 5.3 h per day [22]. In the aforementioned Norwegian study participants aged 65–85 years spend 66% of the day in ST, 24% doing low-intensity PA and 3% doing moderate-to-vigorous physical activity (MVPA) [9].

The variation in the data can be explained by the fact that studies are conducted in different settings and the definition of elderly people varies. Furthermore, there are differences in the assessment of PA data. Some studies are based on measured accelerometer data, others on self-reported data. PA assessment based on self-reporting methods may not quantify PA levels correctly [7]. The use of accelerometer devices for objective assessment of PA allows a valid and reliable record of activity intensity, frequency, and duration which may improve our understanding of PA in the elderly [7, 23].

Individualized feedback on accelerometer measurements can help to increase PA and reduce ST [24–26]. Interventions in promoting PA should consider behavioral-change aspects. A systematic review regarding interventions to promote walking identified two general characteristics of effective interventions. These aspects are *targeting* and *tailoring* and involve addressing participants’ requirements or circumstances [27].

Harris et al. showed statistically significant positive effects in the age group 60–75 years on the amount of PA (average daily step-counts and weekly MVPA in ≥ 10-min bouts) [26]. This intervention included four primary care nurse consultations during a period of 3 months. Participants received feedback on the basis of pedometer step-counts, accelerometer PA intensity, and an individual PA diary and plan. Furthermore, a meta-analyses regarding the impact of pedometer-based physical activity interventions showed that the use of pedometers has a moderate positive effect on PA (an average increase of 2000 steps per day [28]. A systematic review of the use of pedometer interventions showed similar results; participants increased their PA by 2491 steps per day in comparison to the control group [29].

Most previous studies have been characterized by rather complex interventions and also included feedback of PA and ST results, personal consultations, and individual target agreements. A translation of such interventions into real life may be difficult due to considerable costs and effort to reach a large number of people.

Hence, we developed a low-threshold intervention consisting of automatically retrieved, individualized feedback letters, based on accelerometer data. In a randomized controlled trial, the effect of this feedback intervention on the amount of PA and ST will be examined prospectively.

The study protocol follows the Standard Protocol Items: Recommendations for Interventional Trials (SPIRIT) guidelines Additional file 1 [30].

### Research objectives

The primary objective of the MOVING study is to examine the effects of an increase of PA and a reduction of ST after 6 months in the intervention group compared to the control group as assessed by accelerometry.

Secondary outcomes are whether there is an improvement of blood pressure, a reduction in weight and waist circumference as well as an increase of self-reported time doing PA, self-reported ST, and self-reported time doing PA as well as the effect of feedback letters on self-efficacy after 6 and 12 months.

Additionally, the impact of personal feedback letters on lifestyle (household, gardening, free time, and sport activities), quality of life and type of PA will be evaluated by questionnaire in the intervention group compared to control group after 6 and 12 months.

## Methods/design

The study region is Western Pomerania, a rural area in the Northeast of Germany.

MOVING (Motivation-Oriented interVention study for the elderly IN Greifswald) is a two-arm, randomized controlled trial consisting of participant screening, baseline examination, randomization, intervention, and follow-up examinations at 3, 6, and 12 months after baseline. The flow chart of the study is shown in Fig. 1.

**Fig. 1 Fig1:**
[figure not shown]
Flow chart of the study

### Study population

The study population consists of elderly people sampled from the general population who meet the following inclusion criteria:Age ≥ 65 yearsThe possibility of being physically active in daily life

Exclusion criteria are:Permanent use of a wheelchair (no ability to walk independently)Simultaneous participation in other studies including PA or STNot accessible by telephone or cell phone (necessary for screening)Fulfillment of the WHO recommendations for PA (self-report) for people aged ≥ 65 years at baseline

### Recruitment and screening

Participants will be recruited in three ways:Re-contacting participants of a previous study.Participants have given their consent to re-contacting for scientific projectsActive recruitment in general medical practices (GP)Recruitment of volunteers (e.g., in medical practices, hospitals, meeting centers, and via flyers and posters)

Potential participants contact the study staff by telephone or by use of a reply card with contact information. A short telephone screening of potential study participants is performed to assess the inclusion and exclusion criteria. The data will be documented in a documentation system based on electronic Case Report Forms (eCRFs). For participants who meet the inclusion criteria, an appointment for the baseline examination at the examination center of the German Centre for Cardiovascular Research (DZHK) Greifswald is made.

### Baseline examination

At the examination center, the participants are informed in detail about the study and invited to give written informed consent. Upon consent all receive a baseline examination consisting of blood pressure assessment and somatometry data (body weight, waist and hip circumference). All measurements are carried out by trained and certified study staff according to standard operating procedures (SOP).

In addition, all participants receive paper-pencil questionnaires to assess sociodemographics, general health, and actual PA behavior. To asses health status and quality of life the Short Form 8 (SF-8) questionnaire (German version) is used, which consists of eight scales addressing mental and physical health [31].

Furthermore, all study participants will receive the SSA scale (self-efficacy towards physical exercise) to assess each participant’s level of self-efficacy (twelve items which can be summed to a total score in which higher results indicate higher self-efficacy towards PA) [32]. To assess dietary habits, the Mediterranean Diet questionnaire (14 items, score ranging from 0 to 14) will be used [33]. Alcohol consumption will be assessed by using two items from the Alcohol Use Disorders Identification Test (AUDIT) [34].

After answering the questionnaires, all participants receive an accelerometer device (ActiGraph wGT3X-BT, Pensacola, FL, USA). The validated three-axis accelerometer device captures and records continuously PA and ST. Participants are instructed to wear the device during a period of seven consecutive days on the right hip and to remove it only for water-based activities (e.g., showering and swimming) as well as at bedtime. Data will be recorded at a sampling frequency of 30 Hz. Furthermore, participants are asked to document their activities in a semi-standardized daily protocol and to answer several paper-based questionnaires about PA and ST after the 7 days of accelerometer use at home.

To assess self-reported PA, the International Physical Activity Questionnaire short form (IPAQ-SF), German version is used. The IPAQ consists of seven items, addressing intensity and duration of PA in daily life over the last 7 days by self-report [35]. Additionally, the German Physical Activity Questionnaire for 50+ (German PAQ 50+) is conducted to assess type and duration of PA in daily life by self-report [36]. Sedentary behavior is captured by the Measure of Older Adults’ Sedentary Time (MOST Questionnaire) in the German version, which consists of seven items [37] (Fig. 2).

